# A randomized non-inferiority study of low-dose and standard-dose ticagrelor after intervention for acute coronary syndrome: study protocol for the TIGER STUDY

**DOI:** 10.1186/s13063-022-06124-z

**Published:** 2022-03-05

**Keywords:** Acute coronary syndrome, Intervention, Ticagrelor, Dual antiplatelet therapy

## Abstract

**Background:**

Current guidelines recommend that patients with acute coronary syndrome (ACS) who have successfully undergone percutaneous coronary intervention (PCI) should continue to use dual antiplatelet therapy (DAPT) for 12 months. The long-term use of standard-dose dual antiplatelet therapy will increase the risk of bleeding. An optimized antiplatelet strategy that can prevent ischemic events and reduce the risk of bleeding remains to be explored.

**Methods:**

The study is a prospective, multicenter, randomized, open-label, controlled study involving 2090 patients from six clinical centers in China. Through the interactive web response system (IWRS), ACS patients undergoing successful PCI will be randomly divided into the low-dose ticagrelor group or the normal-dose ticagrelor group, after taking 100 mg aspirin and 90 mg ticagrelor bid for 1 week. The primary endpoint is a composite of cardiovascular death, non-fatal myocardial infarction, stent thrombosis, repeat revascularization, and stroke. The secondary endpoints are bleeding events of grade 2 or higher according to Bleeding Academic Research Consortium [BARC] criteria, cardiovascular death, acute myocardium infarction, and coronary revascularization at 1 year.

**Discussion:**

Recent studies have confirmed that 90 mg ticagrelor alone can safely and effectively reduce bleeding without increasing ischemic events of patients with ACS after PCI. Compared with standard-dose DAPT, whether low-dose ticagrelor combined with aspirin can ensure the anti-ischemic effect while reducing the bleeding risk remains unclear in Chinese patients.

The TIGER study will be the first large-scale, multicenter study to compare the efficacy and safety of low-dose and standard-dose ticagrelor combined with aspirin in ACS patients 1 week after successful PCI.

**Trial registration:**

Clinicaltrials.gov NCT04255602. Registered on 5 February 2020.

## Background

Recent guidelines recommended 12-month dual antiplatelet therapy (DAPT) with aspirin and P2Y12 receptor antagonist ticagrelor for ACS patients who undergo PCI with drug-eluting stents (DES) [1, 2]. However, standard-dose DAPT is companied with the incidence of bleeding events to 3–10% [3]. Gastrointestinal hemorrhage is even an independent risk factor for death in ACS patients [4, 5]. The optimized antiplatelet strategy, which could inhibit ischemic events while reducing bleeding events versus standard-dose DAPT, is of vital importance.

Recent clinical trials, such as TWILIGHT and Global Leaders have confirmed that 90 mg ticagrelor alone can safely and effectively reduce bleeding in patients with ACS after PCI [6–8]. Moreover, SMART-CHOICE trial suggested that P2Y12 monotherapy may be a better choice for the Asian ACS population [9]. These studies challenge the current DAPT strategy. However, aspirin should not be given up easily, considering that ticagrelor has a higher rate of discontinuation, the increased frequency of dyspnea, and higher costs than aspirin. Therefore, the optimal DAPT strategy still needs to be explored.

The TIFU study indicated that the low-dose dual antiplatelet drugs may be another choice for ACS patients [10]. PEGASUS-TIMI 54 study and the latest ELECTRA study showed 60 mg ticagrelor has same platelet inhibitory effect as that of 90 mg ticagrelor in patients undergoing PCI [11, 12]. However, larger-scale and high-quality clinical controlled studies are required to confirm these findings.

The TIGER study decided to compare the safety and efficacy of low-dose DAPT (ticagrelor 60 mg bid plus aspirin 100 mg qd) and standard-dose DAPT (ticagrelor 90 mg bid plus aspirin 100 mg qd) following 1-week standard-dose DAPT in ACS patients after successful PCI, aiming to explore the optimal DAPT strategy for ACS patients.

## Methods

### Study objectives and hypothesis

The main purpose of this study is to compare the safety and efficacy of low-dose and standard-dose ticagrelor with aspirin in ACS patients 1 week after successful PCI. We hypothesized that low-dose ticagrelor group would be non-inferior to the standard-dose ticagrelor group in preventing ischemic events while reducing the risk of bleeding.

### Study design and setting

The TIGER study is a prospective, multicenter, randomized, open-label, controlled clinical trial, involving 2090 participants from six heart clinical centers in China. All ACS patients who meet all the enrollment criteria will be randomly assigned to one of the two groups 1 week after the successful PCI: low-dose ticagrelor group (ticagrelor 60 mg + ASA 100 mg; *n* = 1045) and standard-dose ticagrelor group (ticagrelor 90 mg + ASA 100 mg; *n* = 1045), using the interactive web response system (IWRS), at a 1:1 ratio.

All patients will receive standard DAPT (aspirin 100 mg qd + ticagrelor 90 mg bid) therapy in the first week after PCI. Then, patients will take different dose ticagrelor combined with aspirin according to their group within 1 year after surgery. To ensure drug compliance, telephone call will be done monthly by specific staff.

If patients are intolerance to ticagrelor or have ischemic or bleeding complications during the first week after PCI, he or she will be recorded as drop-out and will receive timely and carefully therapy according the exactly situations.

Clinical follow-up will be performed by telephone or office visit at 1 month, 6 months, and 12 months after PCI. The research flow chart is shown in Fig. 1. The follow-up schedule is shown in Table 1.

**Fig. 1 Fig1:**
[figure not shown]
Inclusion flow chart

**Table 1 Tab1:** Follow-up schedule

Follow-up time point (after PCI)	± Days
1 month	20
6 months	20
12 months	20

### Randomization

Our study will strictly follow the principle of randomization. After signing of the informed consent, using the interactive web response system (IWRS) by physician, enrolled patients will be randomly divided into low-dose ticagrelor group (*n* = 1045) and standard-dose ticagrelor group (*n* = 1045). The randomization will be stratified by ACS (STEMI/non-STEMI/UAP), age (< 75/≥75), sex (male/female), and diabetes (yes/no).

### Study population and enrollment criteria

In the TIGER study, a total of 2090 ACS patients receiving successful PCI and 1-week standard-dose DAPT will be enrolled in six cardiac clinical centers. Acute coronary syndrome (ACS) includes ST-elevation myocardial infarction, non-ST-elevation myocardial infarction, and unstable angina [13]. It can be confirmed by clinical symptoms and relevant medical examination. Patients recruited must meet all inclusion criteria and without any exclusion criteria. Patients over 18 years old and less than 90 years old who were diagnosed with ACS and successfully received PCI are eligible for inclusion. The informed consent must be signed before they enter the study. Patients who are allergic to aspirin or ticagrelor cannot participate in the study. Since our study will last 2 years, patients with life expectancy less than 2 years need to be excluded. Meanwhile, considering the impact of pregnancy on individual physiology, pregnant women or women who are going to be pregnant in the next 2 years will not be recruited. Patients with a history of cerebral hemorrhage, stroke within half a year, active hemorrhage, or known hemorrhage diseases will be excluded because of the great risk of bleeding. In order to ensure the compliance and safety of patients, patients with the following conditions should also be excluded, such as several liver and kidney disorders (ALT > 5 times ULA, EGFR < 15 ml/min/1.73 mm^2^), malignant tumor diseases, platelets less than 100 × 10^9^/L or hemoglobin less than 90 g/L, requiring oral anticoagulants, and patients considered unsuitable for this study by the researchers [14, 15]. In all cases, the investigator based on clinical factors and a review of the initial angiogram will make the final decision whether or not to recruit the patient. All the inclusion and exclusion criteria details are described in Table 2.

**Table 2 Tab2:**
[figure not shown]
Enrollment criteria

### Interventions

Antiplatelet drugs are needed to prevent stent thrombosis before and after PCI with DES in ACS patients. If the ACS patient is not taking aspirin before, 300 mg loading dose aspirin must be taken at least 24 h before PCI. Aspirin will then continue to be administered at a dose of 100 mg once daily until 1 year after intervention. Similarly, if the patient did not take ticagrelor, they should use 180 mg loading dose ticagrelor at least 2 h before PCI. Even if patients cannot get ticagrelor 2 h before operation, they will get it in the cardiac catheterization room before it. Within 1 week after the operation, oral administration of ticagrelor 90 mg twice daily should be continuously applied in both groups. Then, patients will be given the corresponding dose ticagrelor (90 mg bid or 60 mg bid) according to the group they entered. The use of aspirin and ticagrelor will last for 1 year after PCI. Notably, additional antiplatelet drugs will not be allowed to use during the period of the study. In our study, only second-generation drug-eluting stents will be used.

### Outcomes

The primary endpoint is the composite endpoint of cardiovascular death, non-fatal myocardial infarction, stent thrombosis, revascularization, and stroke within 1 year after PCI [16]. The secondary endpoints are bleeding events of grade 2 or higher according to Bleeding Academic Research Consortium [BARC] criteria, cardiovascular death, acute myocardium infarction, and coronary revascularization at 1 year [16]. All clinical outcomes are defined according to the Academic Research Consortium (ARC) [17]. All adverse events will be reported to the ethics committee (EC) in a given time. The endpoints will be adjudicated by the Clinical Event Adjudication Committee (CEAC).

### Sample size calculation

In our study, we assume that the composite of MACCE (defined as a composite of all-cause death, myocardial infarction, or stroke at 12 months after PCI) in the control group will be 5% at 1 year in ACS after PCI according to previous studies (STOD-DAPT2, RESET) [18, 19] The inferiority margin was set to 2.5% with clinical considerations. The sample size of the study should not be smaller than 1880 (940 per group) to guarantee 80% power of the study at one-sided significance level of 0.05. Considering 10% of the patients would be lost in the follow-up period, we determined the final sample size to be 2090 patients (1045 per group).

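### The 80% power is calculated for death, MI or stroke, not for the five-component primary endpoint, so it is not shown for the primary test

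*Protocol article*

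**What the plan says.** The sample size section of the protocol article plans on one composite: "we assume that the composite of MACCE (defined as a composite of all-cause death, myocardial infarction, or stroke at 12 months after PCI". The rate attached to it "in the control group will be 5% at 1 year in ACS after PCI according to previous studies". The next sentence reads "The inferiority margin was set to 2.5% with clinical considerations", and the resulting 1880 patients (940 per group) are said "to guarantee 80% power of the study at one-sided significance level of 0.05". Allowing for 10% loss, the total becomes 2090 (1045 per group).

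The Outcomes section defines a different composite: "The primary endpoint is the composite endpoint of cardiovascular death, non-fatal myocardial infarction, stent thrombosis, revascularization, and stroke within 1 year after PCI". The Methods paragraph of the abstract lists the same five components: "The primary endpoint is a composite of cardiovascular death, non-fatal myocardial infarction, stent thrombosis, repeat revascularization, and stroke".

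The Statistical analysis section tests this primary endpoint. It uses a logistic regression adjusted for the stratification factors and compares the upper 90% confidence limit of the odds ratio with the margin.

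The Study design and setting section places randomisation 1 week after PCI. It says that if a patient has "ischemic or bleeding complications during the first week after PCI, he or she will be recorded as drop-out".

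**The concern.** A non-inferiority sample size rests on the control rate and the margin, and both must belong to the endpoint that is tested. Here the planning rate is for all-cause death, MI or stroke. The tested composite narrows death to cardiovascular causes and adds stent thrombosis and revascularization. The planning rate also runs from PCI, whereas randomised patients enter a week later, after those with early ischemic complications have left.

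What is at stake is how the result is read. If non-inferiority is not shown, readers will judge that failure against a claimed 80% power. If it is shown, they will ask whether 2.5 points is an acceptable excess for this composite. The article supports neither judgement, because it gives no rate for the tested endpoint and no reasoning that ties the margin to it.

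**Working it through.** **1. Components side by side**

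| | Sample size section | Outcomes section and abstract | Effect on the rate |
|---|---|---|---|
| Death | all causes | cardiovascular only | lowers |
| MI | included | non-fatal (a fatal MI would count as cardiovascular death) | little change |
| Stroke | included | included | none |
| Stent thrombosis | not included | included | raises |
| Revascularization | not included | included | raises |
| Who is counted | 1-year rate after PCI | patients randomised 1 week after PCI | lowers |

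The changes pull in opposite directions and none is quantified in the document.

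**2. The plan's own figure**

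Inputs from the sample size section: 5% control rate, margin 0.025, one-sided α = 0.05, power 80%. Two readings are not stated there: the low-dose rate is also 5%, and the margin is an absolute risk difference.

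n per group = (z₀.₉₅ + z₀.₈₀)² × 2p(1−p) / margin² = (1.6449 + 0.8416)² × 2 × 0.05 × 0.95 / 0.025² = 6.183 × 0.095 / 0.000625 ≈ 939.8, so 940.

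Allowing for loss: 940 / 0.90 = 1044.4, so 1045 per group and 2090 in total.

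Both match the article exactly. The 80% is therefore the power at a 5% rate, which the article assigns to death, MI or stroke.

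**3. Power at other rates, absolute margin**

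Power = Φ(0.025 / √(2p(1−p)/940) − 1.645), with equal rates in both groups. At 7%: √(2 × 0.07 × 0.93/940) = 0.01177; 0.025/0.01177 = 2.124; 2.124 − 1.645 = 0.479; Φ = 0.684.

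**4. Power at other rates, odds-ratio margin**

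The analysis section tests an odds ratio, but the margin is stated only as 2.5%. As an illustration, convert it at the planning rate: 7.5% against 5% gives (0.075/0.925)/(0.05/0.95) = 1.54. Holding 1.54 fixed is an assumption.

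Approximate power = Φ(ln 1.54 / √(2/(940·p(1−p))) − 1.645). At 7%: √(2/(940 × 0.0651)) = 0.1808; 0.432/0.1808 = 2.390; 2.390 − 1.645 = 0.745; Φ = 0.772.

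**5. Results at 940 per group, one-sided 0.05**

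| Assumed rate, both groups | Absolute margin of 2.5 points | Fixed OR of 1.54 |
|---|---|---|
| 5% | 80.0% | about 65% |
| 7% | 68.4% | about 77% |
| 8% | 63.8% | about 82% |
| 10% | 56.4% | about 88% |

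At 4% the absolute margin gives 86.9%. On that scale power falls as the rate rises; with a fixed odds ratio it rises.

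**6. What 2.5 points means in relative terms**

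(p + 0.025)/p is 1.50 at 5% and 1.25 at 10%. The same absolute margin is a different relative tolerance once the rate changes.

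**The case against.** The strongest reply is that the sample size arithmetic is right and that 5% may still be about right for the tested composite. Restricting death to cardiovascular causes and losing week-1 ischemic events could offset the added components. That offset is possible, and it is why no direction can be claimed. But the article does not argue it: it attaches the 5% to a composite that it defines in full and gives no rate for the other. An unseen analysis plan would not remove a conflict between two definitions that are both printed here.

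A reader might go further and infer that the trial is underpowered. On the absolute scale, 80% power would need 2864 patients at a 7% rate (6.183 × 0.1302/0.000625, so 1288 per group; /0.90, so 1432; × 2) and 3958 at 10%, against 2090. The document does not support that conclusion. Those rates are assumed, the document gives no frequency for revascularization, and the direction reverses under the fixed odds-ratio margin.

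A reader might also infer that the margin was judged clinically for death, MI and stroke. The text says only that clinical considerations were used. The link to that composite comes from the sentence's position and from the exact reproduction of 940, and it is not stated.

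**Conclusion.** The point stands as an inconsistency between sections, not as a calculation error. The 80% is correct for a 5% event rate on an absolute 2.5-point margin, but the article assigns that rate to a composite that is not the primary endpoint. For the tested endpoint, counted in patients randomised a week after PCI, no rate and no power are given.

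How far the true power lies from 80%, and in which direction, is undetermined. Over assumed rates of 5% to 10%, it runs from 80% down to 56% on the absolute margin and from about 65% up to 88% on a fixed odds ratio of 1.54. These figures assume equal true rates, 940 evaluable patients per group, one-sided 0.05 and normal approximations; the odds-ratio figures also ignore covariate adjustment. The mismatch itself needs none of these assumptions.

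**What to change.** Keep the primary endpoint as defined in the Outcomes section and rewrite the sample size paragraph around it:

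- Replace the 5% with a sourced expected rate for the five-component composite, counted from randomisation at 1 week.
- State the margin and its justification for that composite, on the scale that the Statistical analysis section tests.
- Replace the unqualified 80% with the power that 2090 patients give over a range of rates. The event rate pooled over both groups, not split by treatment, may inform that range.

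Settle the margin scale first; otherwise the new power table would again describe a test that is not run.

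Do not switch the primary endpoint to the composite used for planning. The trial is open-label and recruitment was planned to end in February 2022, so a late change would carry its own risk of bias. No further enrolment is proposed.

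The cost is one revised paragraph and a short table. The downside is that the restated power may be less favourable than 80%.

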### Statistical analysis

The efficacy analysis for primary endpoint will be performed in the intent-to-treat population, safety endpoints analyses will be performed in the safety analysis population.

The primary endpoint between groups will be compared with the use of logistic regression, adjusted for the stratification factors (ACS, age, sex, and diabetes). Odds ratio (OR) and the corresponding confidence interval (CI) will be estimated. If the upper limit of the two-sided 90% CI of the OR was less than the prespecified non-inferiority margin, low-dose DAPT strategy will be considered non-inferior to standard DAPT strategy in 1-year period after PCI in ACS patients. Besides, cumulative event rates will be estimated with the Kaplan-Meier method. Patients who were lost to follow-up were censored at the time of the last known contact.

Continuous variable will be descripted as mean (std) or median (interquartile range) as appropriate; categorical variables will be descripted as counts and percentages. *P* values and CIs were 2-tailed except those for non-inferiority testing of the primary end point.

No interim efficacy analysis is planned in this study, an independent data monitor committee (IDMC) will be set up to assess the safety of subjects periodically as previously described.

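### The only stated non-inferiority margin is an absolute 2.5 percentage points, but the decision rule compares an odds ratio with it, so the rule cannot be applied as written and the 80% power belongs to a different test

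*Protocol article*

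**What the plan says.** The Sample size calculation section of the protocol article gives the design inputs. The event rate "in the control group will be 5% at 1 year in ACS after PCI", and "The inferiority margin was set to 2.5% with clinical considerations". The scale of the 2.5% is not named. The size is chosen "to guarantee 80% power of the study at one-sided significance level of 0.05", which leads to 940 per group (1880 in total). After a 10% allowance for loss, "we determined the final sample size to be 2090 patients (1045 per group").

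The Statistical analysis section compares the arms by logistic regression adjusted for the four stratification factors (ACS type, age, sex, diabetes) and estimates an odds ratio. Low-dose treatment is called non-inferior "If the upper limit of the two-sided 90% CI of the OR was less than the prespecified non-inferiority margin". Nowhere does the article give a margin on the odds-ratio scale or a conversion of the 2.5% to that scale.

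**The concern.** A margin and the statistic compared with it must be on the same scale. Here the margin looks like a difference in risks, while the statistic is a ratio of odds whose null value is 1. If so, the trial's single confirmatory decision has no usable criterion in the article, and the power statement describes a test other than the one planned.

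Two things are at stake. First, the criterion would have to be completed later, in an open-label trial. Second, a fixed odds ratio tolerates a different absolute excess of events at each control rate, so the clinical judgement behind 2.5 points is kept only if the control rate is 5%.

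**Working it through.** **Inputs.** From Sample size calculation: control rate 5%, margin 2.5%, power 80%, one-sided alpha 0.05, loss 10%. From Study design and setting: 1:1 allocation. Assumption: the true rate is also 5% in the low-dose arm (the article does not state it).

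**1. Reproduce the plan's figure.** For a risk-difference non-inferiority test,

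n per group = (z₀.₉₅ + z₀.₈₀)² × 2p(1−p) / δ² = (1.645 + 0.842)² × 2 × 0.05 × 0.95 / 0.025² = 939.7, so 940.

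After loss: 940 / 0.9 = 1044.4, so 1045. Both match the article exactly. Other readings do not:
- one-sided alpha 0.025 gives 1194 per group;
- a relative margin (2.5% of 5%, or 0.125 points) gives about 375,900 per group.

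The margin is therefore 2.5 percentage points absolute. The sample-size arithmetic is correct. The confidence level is also consistent, since a two-sided 90% interval matches one-sided 0.05.

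**2. Apply the decision rule literally.** With equal 5% rates and 940 per group:

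| Margin read as | Consequence |
|---|---|
| OR limit < 0.025 | never met (0 of 400,000 simulated trials) |
| OR limit < 1.025 | power about 6% |
| OR limit < 2.5 | power above 99%; tolerates 11.6% v 5%; declares non-inferiority about 79% of the time when the true low-dose rate is 7.5% |

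**3. Convert the margin at the planned rate.** OR = (0.075/0.925) / (0.05/0.95) = 1.54; ln 1.54 = 0.432.

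SE(ln OR) = √(2 / (n p(1−p))):
- n = 940: √(2 / (940 × 0.0475)) = 0.2116; power = Φ(0.432/0.2116 − 1.645) = Φ(0.397) = 65.4% (simulated 65.1%);
- n = 1045: SE = 0.2007; power = Φ(0.508) = 69.4% (simulated 69.2%).

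The risk-difference test has 80.0% at 940 and 83.6% at 1045. For 80% power with an odds-ratio margin of 1.54, n = 2 × 6.18 / (0.0475 × 0.432²) ≈ 1394, so 1395 per group in whole patients, or 1550 per group after 10% loss.

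The margin that would give 80% on the odds-ratio scale at 940 per group is exp(2.486 × 0.2116) = 1.69. At 1045 it is exp(2.486 × 0.2007) = 1.65.

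**4. Vary the control rate.** The rates other than 5% are assumptions, not figures from the article. Power is at 940 per group with equal true rates.

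| Control rate | Excess allowed by OR 1.54 | Power, OR < 1.54 | Power, difference < 2.5 points |
|---|---|---|---|
| 3% | 1.5 points | 48% | 94% |
| 5% | 2.5 points | 65% | 80% |
| 7% | 3.4 points | 77% | 68% |
| 8% | 3.8 points | 82% | 64% |
| 10% | 4.6 points | 88% | 56% |

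**5. Error rate against the absolute margin.** Take 10% v 12.5% (assumed; the true excess is exactly 2.5 points) with 1045 per group. The true OR is 1.286, ln = 0.251, and SE = √(1/(1045 × 0.09) + 1/(1045 × 0.1094)) = 0.139. The probability of declaring non-inferiority under OR < 1.54 is Φ((0.432 − 0.251)/0.139 − 1.645), about 36%. The risk-difference rule gives about 5%.

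**The case against.** *The odds-ratio margin may be stated elsewhere.* The article calls the margin prespecified and cites protocol version 1.1, which is not shown. A reader might infer that no odds-ratio margin exists, or that one will be picked after the data are seen. The document supports neither inference; it shows only that the article states none. The inconsistency still stands, because the article prints both its only margin and its decision rule, and they are on different scales. An odds-ratio margin held elsewhere would also leave open what power belongs to it, since 940 was derived for a risk difference.

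*An odds-ratio test of this size need not be underpowered.* A reader might infer that such a test cannot have 80% power here. That goes too far: at a 5% rate, a margin of about 1.69 gives 80% at 940 per group. The 65% belongs to the direct conversion, 1.54, at 5%. At higher control rates the odds-ratio rule gains power, reaching 82% at 8%. This objection stands, and the power figure must stay conditional on margin and rate.

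*The 36% depends on an assumed 10% rate.* It does, and it is an error rate only if the absolute margin defines the null. The article's own sample size supports that definition. A rate other than 5% is plausible: the 5% is assumed for all-cause death, myocardial infarction or stroke, whereas the primary endpoint in Outcomes adds stent thrombosis and revascularization and counts cardiovascular death only.

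*Covariate adjustment changes power.* It may change it somewhat. It cannot supply a margin.

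**Conclusion.** The point holds. The article's one margin is an absolute 2.5 percentage points, its decision rule is on the odds-ratio scale, and nothing in the article links the two. The rule therefore cannot be applied as written, and the 80% power was computed for a different test. For the odds-ratio rule, power is undefined until a margin is given. Under direct conversion at the planned rate (OR 1.54) it is about 65% at 940 per group and 69% at 1045, assuming equal true 5% rates and an unadjusted log odds ratio. Away from 5% the two criteria diverge: for assumed control rates of 3% to 10%, OR 1.54 tolerates an excess of 1.5 to 4.6 points. Because this is the sole confirmatory criterion, it must be corrected.

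**What to change.** Before any outcome comparison by arm is seen, define the primary test as the low-dose minus standard-dose difference in 1-year event risk. Adjust it for the four stratification factors by standardising the planned logistic model to risks. Declare non-inferiority if the upper limit of the two-sided 90% confidence interval is below 2.5 percentage points. Report the adjusted odds ratio as supportive.

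This keeps the model, margin, alpha and sample size, and the 80% power at a 5% control rate. It has two costs:
- It is a protocol amendment. Under Ethical considerations that means prior written ethics approval, and the article also calls for consent to be signed again after protocol modifications.
- Risk-difference power falls if the control rate is above 5%: about 68% at 7% and 56% at 10%, at 940 per group (assumed rates).

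If the odds ratio is kept as the decision scale, state its margin and restate the power for that margin: about 65% at 940 per group for OR 1.54 at a 5% rate.
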